## **1. STUDY SYNOPSIS**

### **Phase of Development**

Phase 2

### **Objectives**

#### Primary objective:

- To validate the existing demarcation formula (consisting of psychometric and biological markers) which predicts the sensitivity to Lybrido or Lybridos in women with female sexual interest/arousal disorder (FSIAD with or without FOD as secondary diagnosis), measured by the number of satisfactory sexual events (in 150 subjects).

#### Secondary objectives:

- To identify in additional psychometric and biological markers for the demarcation formula in order to increase predictive power for sensitivity to Lybrido or Lybridos in women with female sexual interest/arousal disorder (FSIAD with or without FOD as secondary diagnosis), measured by the number of satisfactory sexual events (in a first set of 75 subjects of the total amount of 150 subjects).
- To evaluate the altered demarcation formula in women with female sexual interest/arousal disorder (FSIAD with or without FOD as secondary diagnosis), measured by the number of satisfactory sexual events (in a second set of 75 subjects).

### **Study Design**

This is a double-blind, randomized, cross-over, placebo-controlled study with a 2-week single-blind placebo run-in period, 3 times 2-week double-blind treatment periods, and a 1-week follow-up period. The double-blind treatment periods consists of a Lybrido (0,50 mg testosterone + 50 mg sildenafil) regime (duration 2 weeks); a Lybridos (0.50 mg testosterone + 10 mg buspirone) regime (duration 2 weeks); and a placebo regime (duration 2 weeks). Each regimen will be separated by at least a 2-day wash out period. Each subject completes the 2-week treatment period in a randomized order according to a Williams design with 6 sequences.

Subjects will visit the study site a total of 7 times: 1 screening visit, 1 start-up visit, 4 study regimen follow-up visits, and 1 final follow-up visit. During the start-up visit and study regimen follow-up visits, the subject's sexual functioning will be evaluated, subject's health will be monitored and study medication will be dispensed (no medication will be dispensed on the last study regimen follow-up visit, V6). Sexual satisfaction will be measured using several questionnaires, some of which will be completed at home following a sexual event. At the start-up visit, the subject will see a psycho-educational DVD with theoretical background information about sexual functioning and fantasizing exercises, to keep the basic knowledge of the subjects about sexuality on an approximately equal level. After watching the DVD the information will be discussed with a psychologist or similar healthcare provider.

The study is divided into a validation part and an exploratory part using two populations. In the validation part, the existing demarcation formula, described elsewhere, will be validated in 150 subjects with FSIAD. In the exploratory part, the possibility of an improved demarcation formula will be investigated using the first 75 of these 150 subjects and then validated in the last 75 subjects.

### **Number of Subjects**

Approximately 150 healthy female subjects with FSIAD will be enrolled and randomized to study treatment.

### **Study Sites and Location**

Up to 2 study sites in the Netherlands will participate to ensure that 150 subjects are randomized to study treatment.

### **Inclusion and Exclusion Criteria**

#### **Criteria for inclusion**

Subjects must meet *all* of the following criteria:

1. Provision of written informed consent
2. Females between 18 and 70 years of age, inclusive, pre- or postmenopausal, with FSIAD (comorbidity with female orgasmic disorder [FOD]; only as secondary diagnosis) is allowed. The diagnosis of FSIAD will be established by a trained health care professional
3. Be involved in a stable, communicative, monogamous relationship and have a sexually functional partner who will be at home for a large part of the study duration
4. Healthy with normal medical history, physical examination, laboratory values, and vital signs; exceptions may be made if the investigator considers an abnormality to be clinically irrelevant
5. Use of highly effective contraception

## **Criteria for exclusion**

Subjects who meet *any* of the following criteria are not eligible to participate in the study:

### Cardiovascular Conditions

1. Any underlying cardiovascular condition, including unstable angina pectoris, that would preclude sexual activity;
2. Systolic blood pressure  $\geq 140$  mmHg and/or diastolic blood pressure  $\geq 90$  mmHg (supine blood pressure). For subjects  $\geq 60$  years old and without diabetes mellitus, familial hypercholesterolemia, or cardiovascular disease: systolic blood pressure  $\geq 160$  mmHg and/or diastolic blood pressure  $\geq 90$  mmHg;
3. Systolic blood pressure  $\leq 90$  mmHg and/or diastolic blood pressure  $\leq 50$  mmHg (supine blood pressure);

### Gynecological and Obstetric Conditions

4. Use of any contraceptive containing anti-androgens (e.g. Cyproteron acetate) or (anti)androgenic progestogens (drospirenone, dienogest, chlormadinone acetate and norgestrel);
5. Use of any contraceptive or hormone replacement therapy (HRT) containing more than 50  $\mu\text{g/day}$  of estrogen;
6. Pregnancy or intention to become pregnant during this study (Note: A urine pregnancy test will be performed in all women of child bearing potential prior to the administration of study medications);
7. Lactating or delivery in the previous 6 months prior to signing Informed Consent Form;
8. History of bilateral oophorectomy;
9. Other unexplained gynecological complaints, such as clinically relevant abnormal uterine bleeding patterns;
10. Perimenopausal status (cycle shortening/irregular menstrual bleeding in the last 12 consecutive months and/or occurrence of vasomotor symptoms (e.g. hot flashes, night sweating) and/or FSH levels ( $>40$  IU/L) for women from age 40 onwards; in women with a history of hysterectomy perimenopausality can be assessed by FSH levels ( $> 40$  IU/L) and/or vasomotor symptoms);

### Other Medical Conditions

11. Liver and/or renal insufficiency (aspartate aminotransferase, alanine aminotransferase and gamma glutamyltransferase > 3 times the upper limit of normal and/or estimated glomerular filtration rate (eGFR) < 60.00 mL/min based on the Cockcroft-Gault formula)
12. Any current endocrine disease or endocrinopathy (e.g. uncontrolled thyroid function) as determined by medical history, basic physical examination and/or laboratory values significantly outside normal range of the central laboratory; or uncontrolled diabetes mellitus (HbA1c > 7.5%)
13. Free- and/or total testosterone levels outside the upper limit of the reference range of the central laboratory;
14. Any current clinically relevant neurological disease which, in the opinion of the investigator, would compromise the validity of study results or which exclude from use of sildenafil, buspirone and/or testosterone;
15. History of hormone-dependent malignancy (including all types of breast cancer);
16. Positive test result for immunodeficiency virus, hepatitis B, or hepatitis C (acute and chronic hepatitis infection);

#### Psychological/Psychiatric Factors

17. History of (childhood) sexual abuse that, in the opinion of the investigator, could result in negative psychological effects when testosterone is administered;
18. (Psychotherapeutic and/or pharmacological treatment for) a psychiatric disorder (other than those under inclusion criterion 6) that, in the opinion of the investigator, would compromise the validity of study results or which could be a contraindication for sildenafil, buspirone and/or testosterone use;
19. Current psychotherapeutic treatment for female sexual dysfunction;
20. Current genito-pelvic pain/penetration disorder according to the Diagnostic and Statistical Manual of Mental Disorders, fifth edition (DSM-5).
21. A substance abuse disorder that, in the opinion of the investigator, is likely to affect the subject's ability to complete the study or precludes the subject's participation in the study;

#### Concomitant Medications

22. Use of potent CYP3A4 inhibitors (eg, ritonavir, ketoconazole, itraconazole, clarithromycin, erythromycin and saquinavir);
23. Use of potent CYP3A4 inducers (eg, carbamazepine, phenytoin, phenobarbital, St John's wort, rifampin);

24. Use of antidepressants including SSRIs, tricyclic and other;
25. Use of any other medication that interferes with study medication (eg, triptans, monoamine oxidase [MAO] inhibitors [includes classic MAO inhibitors and linezolid] and spironolactone);
26. Use of medication (including herbs) that would compromise the validity of study results;
27. Use of testosterone therapy within 6 months before study entry prior to signing the Informed Consent Form;

#### General

28. Illiteracy, unwillingness, or inability to follow study procedures;
29. Participation in other clinical trials within the last 30 days;
30. Any other clinically significant abnormality or condition which, in the opinion of the investigator, might interfere with the participant's ability to provide informed consent or comply with study instructions, compromise the validity of study results, or be a contraindication for buspirone, and/or sildenafil and/or testosterone use.

#### **Test Product, Dose, and Mode of Administration**

*Lybrido* is a fixed-dose combination of testosterone and sildenafil citrate. The drug product is a 9 mm, round, biconvex, white, menthol-flavored tablet for sublingual administration. The outer, polymeric, film coating contains testosterone (0.5 mg) that is released immediately after sublingual administration. The inner core of the tablet contains sildenafil (50 mg). This inner core has a polymeric coating designed to delay release of the sildenafil for approximately 2.5 hours; after this time delay, the sildenafil is released immediately (i.e., it is not a sustained release).

*Lybridos* is a fixed-dose combination of testosterone and buspirone hydrochloride. The drug product is a 9 mm, round, biconvex, white, menthol-flavored tablet for sublingual and oral administration. The outer, polymeric, film coating contains testosterone (0.5 mg) that is released immediately after sublingual administration. The inner core of the tablet contains buspirone hydrochloride (10 mg). This inner core has a polymeric coating designed to delay release of the buspirone for approximately 2.5 hours; after this time delay, the buspirone is released immediately (i.e., it is not a sustained release).

*Placebo* has the exact same appearance and flavor as *Lybrido* and *Lybridos*.

#### **Dosing Instructions**

Subjects will be instructed to keep the tablet under their tongue for 90 seconds and swish the produced saliva beneath their tongues during these 90 seconds, then to swallow the tablet as a whole thereafter, without chewing or otherwise disrupting the dosage form.

A total of 8 doses will be provided for each medication regime; 8 doses Lybrido, 8 doses Lybridos, and 2x (placebo run-in and placebo for double blind regime) 8 doses placebo. Subjects are required to take a minimum of 4 doses over each 2-week treatment regime (2 dose/week). The other 4 doses may be taken as desired (i.e., "on demand") throughout the 2-week treatment regime; dosing is permitted every day until all doses are used. If within a regime a subject uses all doses, medication will not be resupplied.

### **Duration of Treatment**

The trial duration per subject from initial screening through the final follow-up visit is approximately 13 weeks, including a 4-week screening period, a 2-week placebo run-in period, 6 weeks on study medication, and a 1-week follow-up period. In addition, an enrolment period of 16 weeks is anticipated, so the total study duration is expected to be approximately 7 months.

### **Endpoints**

#### Primary Endpoint

Change from placebo in frequency of satisfactory sexual events, following study medication intake, measured by the Sexual Event Diary (SED), item 4. This endpoint will be used for validation of the existing demarcation formula.

#### Exploratory Endpoints

- ◇ Change from placebo in experienced sexually-related personal distress, measured by the Female Sexual Distress Scale-Revised (FSDS-R), specifically item 13.
- ◇ Evaluation of meaningful improvement during treatment period, measured by the single item Patient's Global Impression of Improvement (PGI-I)
- ◇ Evaluation of meaningful benefit of study medication during treatment period, measured by the single item Patient Benefit Evaluation (PBE)
- ◇ Change from placebo in frequency of orgasms, following medication intake, measured by the SED
- ◇ Change from placebo in sexual desire, following medication intake, measured by the SED
- ◇ Change from placebo in physical arousal, following medication intake, measured by the SED
- ◇ Change from placebo in mental arousal, following medication intake, measured by the SED
- ◇ Change from placebo in sexual pleasure, following medication intake, measured by the SED

#### Safety evaluation

- ◇ Adverse events
- ◇ Physical examination (including vital signs)
- ◇ Signs of hyperandrogenism
- ◇ Laboratory assessments (including blood chemistry, hematology and hormone levels)

**Measures for the demarcation formula to predict efficacy for Lybrido and Lybridos:**

A variety of different genetic parameters will be assessed to calculate the current demarcation formula for each individual and to explore an improved demarcation formula for the efficacy of Lybrido and Lybridos. These parameters are based on genetic variations in the, serotonergic, androgen, noradrenergic and other pathways and the stress system, and will be combined with the measurement of hormones (e.g., serum androgen metabolites), second digit to fourth digit ratio and questionnaires regarding sexual functioning.

## LIST OF ABBREVIATIONS

| Abbreviation       | Definition                                             |
|--------------------|--------------------------------------------------------|
| 2D:4D              | second digit to fourth digit ratio                     |
| 3 $\alpha$ -diol-G | 5 alpha-Androstane – 3 alpha- 17 beta-diol glucuronide |
| 5-HT               | Serotonin                                              |
| 5-HT1a             | serotonin 1 alpha                                      |
| 5-HTTLPR           | serotonin transporter-linked polymorphic region        |
| ADT-G              | androsterone glucuronide                               |
| AE                 | adverse event                                          |
| ANOVA              | analysis of variance                                   |
| AR                 | androgen receptor                                      |
| AVP                | arginine vasopressine                                  |
| BMI                | body mass index                                        |
| BOLD               | blood oxygenation level dependent                      |
| bpm                | beats per minute                                       |
| CAG                | trinucleotide (codon): cytosine, adenine and guanine   |
| CAIS               | complete androgen insensitivity syndrome               |
| cGMP               | cyclic guanosine monophosphate                         |
| CRA                | clinical research associate                            |
| CRF                | case report form                                       |
| CRH                | corticotropin-releasing hormone                        |
| DHEA               | dehydroepiandrosterone                                 |
| DHT                | dihydrotestosterone                                    |
| DSM                | diagnostic and statistical manual of mental disorders  |
| DSM-IV-TR          | DSM, fourth edition, text revision                     |
| DSM-5              | DSM, fifth edition                                     |
| DVD                | digital versatile disk                                 |
| ECG                | electrocardiogram                                      |
| eGFR               | estimated Glomerular Filtration Rate                   |
| FOD                | female orgasmic disorder                               |
| FSAD               | female sexual arousal disorder                         |

| Abbreviation | Definition                             |
|---------------------|-----------------------------------------------|
| FSDS-R              | Female Sexual Distress Scale –Revised         |
| FSIAD               | Female Sexual Interest / Arousal Disorder     |
| GC                  | glucocorticoid hormone                        |
| HIV                 | human immunodeficiency virus                  |
| HSDD                | hypoactive sexual desire disorder             |
| 5-HTR1a             | serotonin receptor 1a                         |
| MAO                 | monoamine oxidase                             |
| MC                  | Melanocortin                                  |
| NANC                | Non-adrenergic/Non-cholinergic receptors      |
| NET                 | Norepinephrine transporter                    |
| NO                  | nitric oxide                                  |
| PDE-5               | phosphodiesterase type 5                      |
| POMC                | pro-opiomelanocortin                          |
| SAE                 | serious adverse event                         |
| SAQ-D               | Sexual Anamnesis Questionnaire-Diagnostic     |
| SERT                | serotonin transporter                         |
| SHBG                | sex hormone binding globulin                  |
| SMQ                 | Sexual Motivation Questionnaire               |
| SED                 | Sexual Event Diary                            |
| STAR                | Steroidogenic acute regulatory protein        |
| SUSAR               | suspected unexpected serious adverse reaction |
| VPA                 | vaginal pulse amplitude                       |
| VTA                 | ventral tegmental area                        |

## DEFINITION OF TERMS

**Existing demarcation formula: Sensitivity for sexual cues and maladaptive activity of sexual inhibitory mechanism(s):** The brain's sensitivity for sexual cues and its predisposition for (sexual) inhibitory activity is influenced by the function of the androgen and serotonergic systems and reflected behaviorally as motivational stances towards emotionally relevant cues. Sensitivity to sexual cues and dysfunctional activity of sexual inhibitory mechanism(s) is therefore determined using the following measures:

1. Trinucleotide cytosine-adenine-guanine repeat length of the androgen receptor gene polymorphism (CAG repeat)
2. Serotonin (5-HT) transporter and 5-HT1a receptor genotype polymorphism
3. Androgen metabolites: androsterone glucuronide (ADT-G) and 3-alpha-androstenediol glucuronide (3AG)
4. Second digit to fourth digit ratio (bilateral hand scan)
5. Sexual motivation and inhibition (using the Sexual Motivation Questionnaire [SMQ])
6. Sexual arousal and desire (using the Sexual Anamnesis Questionnaire [SAQ-D])

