**New biomarkers that will be measured to possibly improve the demarcation formula (using microarray chips) are:**

1. Dopamine receptor genotype polymorphism (D1-D5 receptor) and the dopamine transporter
2. All serotonin receptors and the serotonin transporter
3. Corticotropin-releasing hormone (CRH)/ arginine vasopressine (AVP)/ glucocorticoid hormone (GC)/ Melanocortin (MC)/ pro-opiomelanocortin (POMC) receptor genes
4. Noradrenergic transporter (NET), Non-adrenergic/Non-cholinergic receptors (NANC)
5. Oxytocin receptors
6. Prolactin gene polymorphism
7. Steroidogenic acute regulatory protein (STAR), Cytochrome P450 enzymes, Dehydroepiandrosterone (DHEA), Dihydrotestosterone (DHT), Sex-hormone binding globulin (SHBG) gene polymorphism, SHBG receptor polymorphism, aromatase/5-alpha-reductase
8. Nitric Oxide (NO) synthase, Phosphodiesterase type 5 (PDE5) enzymes

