### 2.1.5.2 The existing demarcation formula

In an iterative search process using the data gathered from Studies EB85 and EB70 (see above) a diagnostic working model has been formulated. This model uses an individual's CAG repeat length of the androgen receptor, their 5HT1A receptor genotype, their ADT-G and 3 $\alpha$ -diol-G levels, their 2D:4D ratio, and 5 questionnaire items (from the Sexual Motivation Questionnaire [SMQ] and the Sexual Anamnesis Questionnaire–Diagnostic [SAQ-D]) to investigate their responsiveness to Lybrido and Lybridos.

In our search for a possible relationship between, on the one hand, the above mentioned biological factors, and, on the other hand, the sensitivity for sexual cues (low vs. high) and the responsiveness to Lybrido and Lybridos, we used in our calculations the z-scores of these variables based on 201 study subjects of the EB85 study. Furthermore, we have made use of 41 patients from which we had access to the biological markers (EB85), but also to the results of Lybrido and Lybridos on their sexual satisfaction (EB70) during sexual events.

The aim of our endeavor was to find one demarcation-formula, which could make an optimal differentiation between the effects of Lybrido and Lybridos in our patients. Although we were aware that we would lose information, we took as dependent variable the difference in effect between Lybrido and Lybridos on sexual satisfaction.

In our iterative search-process we used the following (relatively simple) assumptions:  
Firstly, for the supposed influence of the different biological markers on sensitivity to sexual cues, we supposed the following directions:

| Biological marker                         | Low Sensitive Women | High Sensitive Women |
|-------------------------------------------|---------------------|----------------------|
| CAG repeat Androgen receptor              | Long repeat length  | Short repeat length  |
| 2D4D ratio                                | High ratio          | Low ratio            |
| 3 $\alpha$ -diol-G & ADT-G                | Low levels          | Normal/High levels   |
| Serotonin 1A receptor genotype | C variant (CC)      | G variant (GG or CG) |

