#### 4.3.2.2 V1: Start-up Visit

During the start-up visit (V1), subjects will be examined for clinically significant deviations from normal in vital signs. AEs (as defined in Section 5) and concomitant medications will be recorded, monitoring for signs of hyperandrogenism and a urine pregnancy test will be done for all women of child-bearing capability. Also a hand scan of the left hand will be made to measure digit length. The subject will see a psycho-educational DVD with theoretical background information about sexual functioning and fantasizing exercises. After watching the DVD the information will be discussed with a psychologist or similar healthcare provider. Instructions will be given on how to complete the SED and the weekly diary. Subjects will fill out the FSDS-R questionnaire. The first medication bottle will be dispensed to subjects. A blood sample will be taken for the assessment of the biological markers (CAG repeat length of the androgen receptor (AR) gene, SERT, 5-HT1a genotype, and several other markers using microarray chips) if these results are not current within past 12 months and obtainable as part of medical history.

Subjects are expected to complete the full two (2) weeks of the placebo run in period before participating in Visit 2. Subjects may be scheduled for V2 from one day after the end of the placebo run in period and up to one (1) week after the end of that period.

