**Table 4: Measurements and Activities at V1**

#### V1: Start-up Visit

|                                                                  |
|------------------------------------------------------------------|
| Inclusion/exclusion criteria                                     |
| Pregnancy test                                                   |
| Psychoeducational DVD                                            |
| 2D:4D measurement, left hand                                     |
| Vital signs                                                      |
| Collection of blood samples for assessment of biological markers |
| Hyperandrogenism monitoring                                      |

---

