### **4.3.3 Description of Measurements**

#### **4.3.3.1 Hand Scan Measuring Digit Ratio**

Subjects will be asked to remove any jewelry or rings that would interfere with obtaining finger length measurements (subjects who are unable to remove rings will be asked to slide the jewelry up the digit as far as possible to allow documentation of the digit/hand intersection). Each subject's left hand will be scanned using a standard photo scanner at a resolution of 200 dpi. The subject will be instructed to place the ventral surface of their hand lightly on the surface of the scanner, with the second to fifth fingers held parallel and the tip of the middle finger aligned with the wrist and elbow. Scanned hand images will be analyzed using computer-assisted image analysis software. A built-in measurement tool (accurate to 0.1 mm) will be used to measure digit length. The length of the second and fourth digit of the left hand will be measured from the ventral proximal crease of the digit to the tip.

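### The existing formula is defined with a bilateral 2D:4D ratio, but the trial measures the left hand only

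*Protocol*

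**What the plan says.** **Hand.** The itemised definition of the existing formula (Definition of Terms) includes "Second digit to fourth digit ratio (bilateral hand scan"). The places that tell the site what to do differ from it:

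- Section 4.3.2.2 (V1): "Also a hand scan of the left hand will be made to measure digit length".
- Table 4: "2D:4D measurement, left hand". Appendix 2 carries the same entry at V1.
- Section 4.3.3.1: "Each subject's left hand will be scanned using a standard photo scanner at a resolution of 200 dpi". The digit lengths that it goes on to specify are likewise those of this one hand.

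Section 2.1.5.2, which describes how the formula was built, names the 2D:4D ratio as an input but no hand.

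**Serotonin marker.** Definition of Terms gives the existing input as "Serotonin (5-HT) transporter and 5-HT"1a receptor genotype. Section 2.1.5.2 gives a list that begins "This model uses an individual's CAG repeat length of the androgen receptor" and contains the 5-HT1A genotype but not the transporter; the two tables in that section also show only 5-HT1A. The list of new candidate markers in Definition of Terms has "All serotonin receptors and the serotonin transporter".

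**The concern.** The primary objective is to validate a score that already exists, so the trial must apply it with the inputs it was derived with. Those inputs were converted to z-scores on 201 EB85 subjects (section 2.1.5.2). A reference mean and SD for a two-hand ratio do not automatically fit a left-hand ratio.

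The score does two jobs in section 6.3: it forms the low- and high-sensitivity groups for the ANOVA, and it is the predictor in the ROC analysis. The planning support in section 6.1 (a 48%/52% split and a correlation of .83) comes from earlier use of the formula and carries over only if the score is the same.

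The hand matters most because it concerns data collection. The SAP can settle wording, weights and cut-offs, but it cannot supply a measurement that was never taken.

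The transporter raises a smaller question. The secondary objectives compare an altered formula with the existing one, and that comparison reads cleanly only if it is clear which markers belong to the existing one.

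**Working it through.** **1. Hand: the passages side by side.** One place says both hands (Definition of Terms). Four places say left hand (4.3.2.2, Table 4, 4.3.3.1, Appendix 2). One place is silent (2.1.5.2). Both versions cannot be right, and the protocol does not show which hand EB85 used.

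**2. Transporter: the passages side by side.** It is in the existing formula (Definition of Terms), absent from it (2.1.5.2 and its tables), and on the new-marker list (Definition of Terms). The repeat of that new list in 2.1.6 names the serotonin receptors without the transporter. On data, section 4.3.2.2 names SERT among the markers from the V1 blood sample. Appendix 3 has no SERT row, but it has a microarray row and refers to Definition of Terms for that row's content, which includes the transporter. The data are therefore planned.

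**3. The plan's own figure.** Section 6.1 states 90% power for AUC 0.65 against 0.5, with 75 + 75 women and alpha .05. With the Hanley-McNeil variance:

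- Var(A) = [A(1−A) + 74(Q1−A²) + 74(Q2−A²)] / 75², where Q1 = A/(2−A) and Q2 = 2A²/(1+A).
- At A = 0.5: (0.25 + 74 × 0.16667)/5625 = 0.002237, SE 0.0473.
- At A = 0.65: (0.2275 + 74 × 0.1486)/5625 = 0.001995, SE 0.0447.
- Power, two-sided = Φ[(0.15 − 1.96 × 0.0473)/0.0447] = Φ(1.28) = 0.900.

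The stated 90% reproduces, so the sample size is not in dispute here. One-sided alpha .05 would give 0.947; two-sided is used below because it matches the stated figure.

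**4. Size if the wrong hand is used.** Nothing in the documents gives this, so it rests on these assumptions:

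- The inputs are equally weighted, independent z-scores.
- k = 5 to 10 inputs. Section 2.1.5.2 lists five biological inputs, plus five questionnaire items.
- The left-hand ratio correlates r = 0.6 to 0.9 with the bilateral ratio.
- The intended score has AUC 0.65, and the left hand adds no information of its own.

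Score correlation c = (k − 1 + r)/k:

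- Lowest (k = 5, r = 0.6): 4.6/5 = 0.92.
- Highest (k = 10, r = 0.9): 9.9/10 = 0.99.

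Share of women changing sign, for two standard normal scores = arccos(c)/π:

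- c = 0.92: 0.403/3.1416 = 0.128; × 150 = 19 women.
- c = 0.99: 0.1415/3.1416 = 0.045; × 150 = 7 women.

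Attenuated AUC under a binormal model: d = √2 × z(0.65) = 0.545; ρ = d/√(d² + 4) = 0.263; d′ = 2ρc/√(1 − ρ²c²); AUC′ = Φ(d′/√2). Power is as in step 3.

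- c = 0.92: AUC 0.638, power 84.1%.
- c = 0.99: AUC 0.648, power 89.4%.

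**The case against.** The formula predates this trial, is described elsewhere according to section 3.4, and was already used for inclusion in EB82 and EB90. Four operational places agree on the left hand against one parenthesis in a definitions list, so a slip in that list is at least as plausible as a changed input. This stands: a change of score is not shown. It does not remove the conflict, because the protocol alone does not say which version is right, and one of the two possibilities costs data.

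A reader might infer more in four ways, and the documents do not support them:

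- *That the score also cannot be computed for want of the transporter.* SERT is named in the V1 blood sample and the transporter is on the microarray panel. A missing separate row in Appendix 3 is not a missing assay. Power figures that assume both inputs differ (77% to 86%) therefore do not describe an established data gap.
- *That appearing on the new-marker list proves the transporter is outside the existing formula.* The same entry covers all serotonin receptors, hence 5-HT1A, which is undisputedly an existing input.
- *That the whole formula is cut at zero.* Section 2.1.5.2 states the sign rule for the Stroop task and the biological part; the decision tree for the full formula is in a figure not shown. The ROC analysis, the only one powered in section 6.1, varies the cut-off. Reclassification at zero would affect the ANOVA groups, not the AUC.
- *That a fifth of the women would change class.* That needs a score correlation near 0.8, which is below what substituting one hand gives on the assumptions above.

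**Conclusion.** The conflict over the hand is real and stands in the current text. It concerns the score named in the primary objective and, on one of its two readings, a measurement that cannot be made good afterwards. That makes it more than clerical, but it does not show that the trial will validate a different score.

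The likely size is modest: score correlation 0.92 to 0.99, about 7 to 19 of 150 women reclassified if a zero cut-off applies, and power of about 84% to 89% against the planned 90%. All of this rests on equal, independent inputs and an assumed left-versus-bilateral correlation of 0.6 to 0.9. If the derivation used the left hand, the effect on the score is nil and only the definition needs correcting.

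The transporter's status is inconsistent too, but that is a matter of wording, since data on it are planned in any case.

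**What to change.** 1. Check which hand or hands the EB85-derived 2D:4D z-score used. If both, scan both hands at V1 and amend 4.3.2.2, Table 4, 4.3.3.1 and Appendix 2. If the left only, replace bilateral with left hand in Definition of Terms.
2. State once whether the serotonin transporter is an input to the existing formula, and make Definition of Terms (both lists), 2.1.5.2, 2.1.6, 4.3.2.2 and Appendix 3 agree, so that the existing and altered formulas are clearly separated.

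The check should come before the first V1. The cost is a wording change and, if both hands are needed, about a minute per woman on the same scanner (an estimate, not a protocol figure). No new equipment, visit or blood sample is required.
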